### Data analysis

In the quantitative component, descriptive statistics will be used to summarise the demographic information of participants and to provide an overview of the recruitment rate, retention rate, attendance rate and scale completion rate. This will involve calculating means, SD, frequencies and percentages.^54^ The scale completion rate will be assessed by determining the proportion of scales completed in full by participants. To examine the differences in outcomes before and after the intervention, independent sample t-tests will be employed to compare the change scores from the pretest to the post-test. In the qualitative component, thematic analysis will be used to analyse data collected from both qualitative interviews and focus groups.^55^ The content of interviews with older people and focus groups with staff and young people will be examined to identify themes related to the acceptability of the intervention. Findings from the quantitative and qualitative components will be brought together during interpretation to inform a comprehensive understanding of feasibility and acceptability.

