**Methods and analysis:**

Our study employs an embedded mixed-methods design, integrating quantitative measures with qualitative insights, to assess the feasibility and acceptability of a 5-week intergenerational engagement intervention in a long-term care facility in China. Quantitative data will include recruitment, retention, attendance and scale completion rates, using descriptive statistics and independent sample t-tests to compare preintervention and postintervention outcomes. Qualitative data will be gathered through individual interviews with older participants and focus groups with staff and young people and will be analysed thematically to explore themes related to intervention acceptability. Integration will be undertaken at the interpretation stage, where findings from both components will be compared and synthesised to provide a comprehensive evaluation of the intervention.

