### Study participants

#### Older people

This feasibility study will recruit 30 older people residing at the study site for the IE study. Eligibility criteria for older people will include: (1) aged 60 years or above; (2) in relatively good physical and mental health, able to perform daily activities with minimal assistance and actively participate in the study without requiring intensive medical or psychological support; (3) able to communicate effectively in either Cantonese or Mandarin, including understanding, responding to questions and engaging in conversations and (4) willing to participate in the IE programme and provided signed informed consent.

Older people will be excluded if they: (1) have medium or severe cognitive impairments, experiencing an acute phase of a chronic disease, have severe physical disabilities (eg, bedbound) or were in the end-of-life period; (2) were unable to communicate effectively in either Cantonese or Mandarin and (3) declined to provide informed consent or expressed unwillingness to engage in the IE programme.

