### Data collection

#### Before the intervention

Baseline demographic data will be collected from older people, including age, gender, education level, marital status, living support and health conditions. They will also invite to complete four scales: CGDS-11, GAI-CV, DJGLS and SF-12. The entire data collection process takes 35–40 min. For staff and young people, only demographic data will be collected.

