#### After the intervention

In the quantitative component, older people will complete the following four scales as a post-test: CGDS-11, GAI-CV, DJGLS and SF-12. This will be conducted within 7 days after the intervention to assess its immediate feasibility results before potential external effects can have an impact.

In the embedded qualitative component, we will capture valuable insights into the acceptability of the intervention through interviews and focus groups. For older people, semistructured individual interviews will be conducted to explore their experiences, with each interview lasting 30–45 min. For staff and young people, focus groups will be organised, with each session expected to last between 60 and 90 min.

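### Independent-sample t-tests are named for before/after scale scores, although one group of older people supplies both measurements and there is no comparison group

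*Protocol article*

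**What the plan says.** The protocol article names the test twice.

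- Data analysis: the purpose is given as "To examine the differences in outcomes before and after the intervention", and for this "independent sample t-tests will be employed to compare the change scores from the pretest to the post-test".
- Abstract, Methods and analysis: the quantitative work is described as "using descriptive statistics and independent sample t-tests to compare preintervention and postintervention outcomes".

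The people who supply scores are described in three places.

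- Study participants, Older people: "This feasibility study will recruit 30 older people residing at the study site for the IE study".
- Data collection, Before the intervention: of the older people it says "They will also invite to complete four scales: CGDS-11, GAI-CV, DJGLS and SF-12". The same paragraph limits data from staff and young people to demographics.
- Data collection, After the intervention: "older people will complete the following four scales as a post-test: CGDS-11, GAI-CV, DJGLS and SF-12", within 7 days of the programme's end.

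No control arm, randomisation or subgroup contrast is described, and no paired test is mentioned.

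**The concern.** An independent-sample t-test compares two separate sets of people. Here one set of people is measured twice, so neither statement of the test suits the data. The literal wording leaves the analyst with nothing to compare. The abstract's wording can be computed, but it treats two scores from one resident as if they came from two residents.

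This is the only inferential test in the article, and it is applied to the depression, anxiety, loneliness and quality-of-life scores. If the abstract's version were run, the P values would be too large whenever a resident's two scores are positively correlated, and a real change could be missed. The study is also meant to inform a later trial, for which the mean and SD of within-person change are the useful quantities. The named test is not built on that SD.

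**Working it through.** **Step 1: is there a second scored group?** The article's total is 50 participants. The parts are 30 older people, 15 young people and 5 staff: 30 + 15 + 5 = 50. The stated total is reproduced and leaves no unallocated participants. Of the three parts, only the 30 older people complete the scales. There is one scored group.

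**Step 2: the Data analysis wording.** A change score is post minus pre for one resident. Thirty residents give at most 30 change scores, all in one sample. A two-sample test needs a second sample of change scores, and none exists. On this reading the test cannot be run and yields no P value.

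**Step 3: the abstract wording.** Take n = 30 complete pairs, the same SD at both times, and pre-post correlation r.

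- Treated as independent: SE = SD × sqrt(2/n) = SD × sqrt(2/30) = 0.258 SD, with 2 × 30 − 2 = 58 df.
- Paired: SE = SD × sqrt(2(1 − r)/n), with 30 − 1 = 29 df.
- Ratio: sqrt(2/n) / sqrt(2(1 − r)/n) = 1/sqrt(1 − r).

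The article gives no pre-post correlation, so r is an assumption and is shown as a range. The only related figure is the test-retest reliability of 0.712 quoted for CGDS-11 in the Outcomes section. It is used here as a guide for that scale alone. Type I error was obtained by simulation: 50,000 bivariate-normal replicates per setting, no true change, nominal two-sided level 5% (also assumed, since the article states none).

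| Assumed r | SE, independent (SD units) | SE, paired (SD units) | Ratio | Type I error, independent | Type I error, paired |
|---|---|---|---|---|---|
| 0 | 0.258 | 0.258 | 1.00 | 0.0501 | 0.0501 |
| 0.3 | 0.258 | 0.216 | 1.20 | 0.0203 | 0.0499 |
| 0.5 | 0.258 | 0.183 | 1.41 | 0.0065 | 0.0479 |
| 0.712 | 0.258 | 0.139 | 1.86 | 0.0006 | 0.0485 |
| 0.8 | 0.258 | 0.115 | 2.24 | 0.0001 | 0.0499 |

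The two tests agree only near r = 0. The paired test holds its level throughout, apart from simulation error.

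**Step 4: the consequences are alternatives.** Step 2 follows from the Data analysis wording and step 3 from the abstract's. They do not add up, because only one reading can be followed.

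**The case against.** The best defence is that little depends on this test. The aim is feasibility and acceptability. The Study design section says the quantitative data will be analysed descriptively, the Outcomes section introduces the scales under completion rate, and the Sample size section says such studies assess practicality rather than effectiveness. No progression rule in the article uses a P value. If the same residents contribute at both times, the mean difference is identical under either test. All of this stands, and it limits the size of the point.

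A second defence is that a paired test was meant. The reference to change scores makes that plausible, but the article names the wrong test in two places. An analysis plan that is not shown cannot excuse a test stated wrongly here.

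A third possibility is an undescribed second arm. Figure 1 is not available, and the Sample size section mentions two groups of participants sharing the activity room. In context these are most naturally the older and the young people, and nothing in the text points to a second group with scale scores.

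Some stronger conclusions are tempting but unsupported:

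- A reader might infer that planned confidence intervals for the scales will be wrong. The article plans none; it names only t-tests.
- A reader might infer that within-person change is thrown away altogether. The Data analysis section does form change scores; it is the named test that does not fit them.
- A reader might take the factor of 1.86 as the size of the error. It rests on one scale's test-retest value, which is not a pre-post correlation across a 5-week programme. No comparable test-retest figure is given for the other three scales.

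**Conclusion.** The test is wrong as written, in both the abstract and the Data analysis section. Depending on which wording is followed, it either cannot be run or ignores the pairing. In the second case the standard error is 1.20 to 2.24 times too large for r from 0.3 to 0.8, and the actual type I error is about 2% down to 0.01% instead of 5%. At r = 0.712 the figures are 1.86 times and about 0.06%. These sizes assume 30 complete pairs, equal SDs, normal scores and a positive correlation that the article does not state.

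A reader might infer that the study risks false-positive findings or that its feasibility conclusions are unsafe. Neither follows. With positive r the error is conservative, and the recruitment, retention, attendance, completion and qualitative results do not use the test. The correction is still needed, because a named test that does not match the design should not stand when two changes of wording would put it right.

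**What to change.** In the abstract's Methods and analysis paragraph and in the Data analysis section, replace the independent-sample t-test with a paired t-test (equivalently, a one-sample t-test on within-person change). State that it is applied to older people with both measurements, and that the mean change, its SD and a 95% CI will be reported for each scale. Restricting to complete pairs matters because the article expects possible dropout: an unpaired comparison could include baseline scores of residents with no post-test, and so mix change with attrition. A Wilcoxon signed-rank check is optional and not needed to correct the error.

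The cost is the rewording of two sentences. The same residents are already due to be measured at both times, so no new data are required.

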## Ethics and dissemination

The study received approval from the Ethical Review Committee of the University of Birmingham (ERN_1775-Jul2024). Relevant local ethical approval was also obtained from the Ethics Committee of Guangzhou Furuixin Senior Apartment in China, approved in July 2024. The feasibility study was registered with the ISRCTN registry (ISRCTN14922432). Confidentiality and data protection measures are strictly adhered to throughout the study. The primary research paper will be submitted to peer-reviewed journals to contribute to the growing body of evidence on the use of IE in LTC facilities in China. A final report will be written and published on completion of the study. The results will be disseminated through peer-reviewed journals and shared through presentations at relevant conferences and meetings. These efforts aim to maximise the impact of the research and inform future practices in LTC facilities in China.
